### Masking

3.6

The principal investigator, study investigators, laser instrument operator, participants, outcome assessors, and biostatistician will all be blinded to the treatment assignments between real and sham laser moxibustion. Only outcome assessors and the statistician will be blinded as to whether the patient receives real/sham laser moxibustion or waitlist control.

The laser instrument for the sham group is designed so that the participants will not receive complete warmth at the site of application. While some participants in the ILM group will feel warm, these 2 groups will be treated separately so that they will not have a chance to communicate. At the end of the intervention period, participants and operators in ILM or SILM will assess the masking. They will be asked to guess their group assignment.

### Outcome measures

3.7

Outcome measures and data collection time points are listed in Table 2. The primary endpoint of this study is the post-intervention assessment (T2, after 6 weeks of treatment sessions). We will measure primary and secondary outcomes at baseline (T0), mid-intervention (T1, after 3 weeks of treatment sessions), post-intervention (T2) and at follow-up (T3 and T4, 6, and 12 weeks after 6 weeks of treatment sessions). The collected clinical data will be collected with REDCap.

**Table 2 T2:**
[figure not shown]
Data collection time points of all outcome measures.

#### Primary Outcome

3.7.1

Our primary outcome is the fatigue score measured by the Chinese version of the Brief Fatigue Inventory (BFI-C).^[30,31]^ The scale score has excellent internal consistency of 0.96. The indicators of the scale assessment include the current level of fatigue; the fatigue level within the past 24 hours; and the impact of CRF on physical activities, emotions, ability to walk, ability to work, relationships with others, and enjoyment of life within the past 24 hours. The BFI-C uses 10-point numeric descriptions: scores of 1 to 3 represent mild levels of fatigue, scores of 4 to 6 represent moderate levels of fatigue, and scores of 7 to 10 represent severe levels of fatigue. The endpoint is the change in fatigue score from Baseline to Week 6 (end of treatment) among the 3 groups.

#### Secondary outcomes

3.7.2

##### Quality of Life (QOL)

3.7.2.1

We will use the Chinese version of the Functional Assessment of Cancer Therapy-Breast (FACT-B) to measure quality of life in BCS. The FACT-B is a breast-specific module comprised of the original four subscales of the Functional Assessment for Cancer Therapy - General (FACT-G) scale: physical well-being, functional well-being, emotional well-being, and social/family well-being, adding a breast cancer-specific subscale.^[32]^ It is a 37-item instrument and each question is rated on a 5-point Likert scale. Higher scores represent improved global QOL.^[33]^ The simplified Chinese version of the FACT-B is validated and reliable for Chinese breast cancer patients with a Cronbach's α of >0.80 in most domains except in additional concerns (0.59).^[34]^

##### Depression/Anxiety

3.7.2.2

We will use the Chinese version of the Hospital Anxiety and Depression Scale (HADS) to measure anxiety and depression symptoms in BCS. The HADS is a brief 14-item instrument, with seven items in each of the anxiety and depression scales scored from 0 to 3, resulting in scale scores ranging from 0 to 21.^[35]^ Established cutoffs are: 0 to 7, not significant; 8 to 10, subclinical; and 11 to 21, clinically significant depression/anxiety. The Chinese version of HADS is a reliable and valid measure of both anxiety and depression in cancer patients with Cronbach α ranging from 0.86 to 0.93.^[36]^

### Stress

3.8

We will use the Chinese version of 10-item Perceived Stress Scale (PSS-10) to measure stress in BCS. The PSS-10 is a shortened version of the original 14-item version and psychometrically superior to it with a Cronbach's α >0.70 are usually recommended.^[37]^ Each question in this 10-item instrument is rated on a 5-point Likert scale (0 = never to 4 = very often). A higher score indicates greater stress.

### Insomnia

3.9

We will use the Chinese version of the Pittsburgh Sleep Quality Index (PSQI) to assess sleep disturbance in BCS. The PSQI is a 19-item self-report instrument that includes seven component scores: subjective sleep quality, sleep latency, sleep duration, habitual sleep efficiency, sleep disturbances, sleep medication, and daytime dysfunction.^[38]^

The scores for these components range from 0 (no difficulty) to 3 (severe difficulty), with a higher score denoting poorer sleep quality (range: 0–21). It suggests a global score cut-off of 8 for the presence of sleep disturbance in cancer patients and has a Cronbach α of 0.79.^[39]^

### Pain

3.10

We will use the Chinese version of the Brief Pain Inventory (BPI) to assess cancer pain. The BPI is an 11-item self-administered questionnaire that includes two main scores: a pain severity score (scored from 0 to 10, ranging from 0 to 40) and a pain interference score (scored from 0 to 10, ranging from 0 to 70).^[40]^ The Chinese version of the BPI is a reliable and valid measure of both the severity and impact of pain in cancer patients, with Cronbach α of 0.894 and 0.915, respectively.^[41]^

### Laboratory examination

3.11

We will collect 6-mL ethylenediamine tetra-acetic acid tubes of blood from participants at T0, T2. We will process these samples and store them into −80°C feezer within 24 hours of collection. Then we will prepare the blood samples to evaluate leukocyte genomic DNA telomere length and cortisol.

### Assessment of treatment expectancy

3.12

We will modify the Chinese version of the Acupuncture Expectancy Scale (AES) to assess response expectancy of laser moxibustion at T0, T1, and T2 (end of intervention). The AES is a 4-item instrument designed to assess outcome expectancy in acupuncture clinical trials, each with a 5-point Likert scale ranging from 1 to 5. The scores range between 4 and 20, with a higher score indicating greater expectancy. It has demonstrated reliability (Cronbach α of 0.82) and validity and is positively correlated with patient self-reported efficacy and satisfaction.^[42]^

### Assessment of adverse events

3.13

We will monitor patients for adverse events (AEs) during the study period and record any incidents in the case report forms. At the post-intervention (T2), a research assistant will collect information from patients about whether they have experienced or are experiencing AEs during the intervention (ILM or SILM) period. The principal investigator or treating clinician will assign the attribution of the AEs.

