### Study design

3.1

We will conduct a randomized controlled, 3-arm trial of ILM compared to SILM and WLC for moderate (score of 4–6 on BFI-C) to severe (score of 7–10) fatigue in BCS. After random assignment to 3 groups, patients in the ILM and SILM groups will receive 20-minute treatments of real/sham infrared laser moxibustion twice per week for six weeks. We will have a 12-week follow-up period to evaluate the durability of the treatment effects. We will assess patient-reported fatigue and other comorbid symptoms at Baseline, Weeks, 6, 12, and 18, respectively. We have included details of the study timeline in Figure 1. This study was approved by the Institutional Review Board of Yueyang Hospital and registered with the identifier NCT03553355 (12 June 2018) at ClinicalTrials.gov. All participants will provide written informed consent.

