### Criteria for discontinuation

3.14

Every effort will be made to retain patients in the trial and to minimize withdrawals. However, the trial will be discontinued on condition that any serious adverse events happen. Additionally, patients may request to be withdrawn from this study at any time without any reason.

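### The only scheduled adverse-event enquiry described is at T2 and is worded for the ILM or SILM period, so events may be ascertained unequally between laser and waitlist arms and between treatment and follow-up

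*Protocol article*

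**What the plan says.** Section 3.13 (Assessment of adverse events) has two layers. The first is general: "We will monitor patients for adverse events (AEs) during the study period and record any incidents in the case report forms". It is not limited to particular arms and it runs past Week 6, but it gives no method.

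The second is a specific procedure, carried out by a research assistant at T2 (Week 6). The question put to patients there is "whether they have experienced or are experiencing AEs during the intervention (ILM or SILM) period". No other adverse-event enquiry is named in the text. On causality, the section adds: "The principal investigator or treating clinician will assign the attribution of the AEs".

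Three other sections bear on the point:

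- Section 3.5.3 states that waitlist participants get neither real nor sham laser during the study.
- Section 3.1 states: "We will have a 12-week follow-up period to evaluate the durability of the treatment effects".
- Section 3.7 schedules outcome assessments at baseline, "mid-intervention (T1, after 3 weeks of treatment sessions), post-intervention (T2) and at follow-up (T3 and T4, 6, and 12 weeks after" the six treatment weeks. That puts T3 at Week 12 and T4 at Week 18.

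**The concern.** Asking everyone a set question usually brings out more events, especially mild ones, than recording whatever comes to light. If the question is put only to patients who have had a laser or sham period, those two arms gain a source of events that the waitlist arm lacks. The same holds within the laser arms for the treatment weeks compared with follow-up.

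The waitlist arm is the only one that can show how often these women have symptoms with no device session at all. The Discussion says the group was added to estimate the overall effect of laser moxibustion, and it expects fatigue to occur together with pain, poor sleep and mood symptoms. Background events should therefore be common enough for the way of asking to matter. If they are solicited in one place and not in another, laser can look less safe than no treatment for reasons unrelated to the device.

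Two features add to the asymmetry. Laser participants attend 12 sessions (Section 3.5.1), which are further occasions to mention a symptom, and waitlist participants attend none. Also, under Section 3.6 only outcome assessors and the statistician are blinded to laser versus waitlist, so the principal investigator or clinician who attributes events is not.

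**Working it through.** The plan gives no figure on this point, so there is none to reproduce. The check compares the wording with the arms and weeks of the trial, and then shows what a bias would look like under stated assumptions.

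**Coverage of the T2 enquiry as worded**

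Inputs: 140 randomised 2:2:1 (Section 3.15), six treatment weeks, and 12 follow-up weeks (Section 3.1).

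- Arms: 140 × 2/5 = 56 ILM, 56 SILM, and 140 × 1/5 = 28 waitlist.
- Patients with an ILM or SILM period: 56 + 56 = 112 of 140. The other 28 (20%) have none.
- Weeks covered: 6 of 18 (33%).
- Planned person-weeks covered, before attrition: 112 × 6 = 672 of 140 × 18 = 2,520, which is 27%.
- Person-weeks outside the enquiry: 28 × 18 = 504 in waitlist, plus 112 × 12 = 1,344 in laser follow-up, total 1,848. These fall under the general monitoring sentence only.

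**Possible bias in laser versus waitlist over six weeks**

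Assumptions, none of them from the documents: the true proportion with a reportable event is 20% in every arm, capture in the laser arms is 70–100%, and capture in waitlist is 30–70%.

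Formula: false excess = 0.20 × (laser-arm capture − waitlist capture).

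| Laser-arm capture | Waitlist capture | False excess |
|---|---|---|
| 100% | 30% | 0.20 × 0.70 = 14 points |
| 100% | 70% | 0.20 × 0.30 = 6 points |
| 70% | 30% | 0.20 × 0.40 = 8 points |
| 70% | 70% | 0.20 × 0 = 0 points |

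In counts, each laser arm would truly have 56 × 0.20 = 11.2 women with an event and would record 7.8 to 11.2. Waitlist would truly have 28 × 0.20 = 5.6 and would record 1.7 to 3.9.

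**ILM versus SILM to Week 6**

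Both arms get the same question at the same time about the same period, and the session schedule is the same. Capture is equal by design, so the formula gives zero.

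**The case against.** The strongest objection is that the first sentence of Section 3.13 already covers every arm and the whole study. That stands against a stronger inference a reader might draw: that the waitlist arm and the follow-up weeks have no comparable safety data, or that events there are caught only when volunteered. The documents say neither. The method of general monitoring is not stated and could include asking at visits.

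A second objection is that Table 2 and Figure 1 are not shown and the article condenses a fuller protocol, so an adverse-event entry at other visits cannot be ruled out. That also stands: it cannot be asserted that patients are asked only once. It does not remove the point, because the article is not silent. It names a time point and two arms. If another part of the plan schedules the enquiry more widely, Section 3.13 needs to be reconciled with it.

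Third, neither the aims nor the analysis section plans an adverse-event comparison with waitlist. The specific contrast is ILM versus SILM, and that is sound to Week 6. No laser is given in Weeks 7 to 18, and the likely bias runs against the device, so it would not hide harm. All of this limits the consequence. Even so, events in a three-arm trial are likely to be read by arm, and such a reading would be unsafe.

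A reader might also infer that unequal capture makes the rule that "the trial will be discontinued on condition that any serious adverse events happen" depend on the arm. The documents do not support that. The rule is not tied to the T2 question, general monitoring applies to all arms, and serious events are more likely than mild ones to surface unprompted.

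**Conclusion.** The point holds in a limited form. Section 3.13 describes one scheduled enquiry and words it so that it fits two of the three arms and six of the 18 weeks. Followed literally, it produces solicited events in the laser arms with no like-for-like counterpart in waitlist or in follow-up. A laser versus waitlist comparison of adverse events may then be biased, probably against laser.

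The size is unknown. The illustrative range of 0 to 14 percentage points rests entirely on the assumed 20% event rate and the assumed capture ranges. A narrower claim of 6 to 14 points would be tempting, but it requires complete capture in the laser arms, which a six-week recall can hardly be presumed to give. With 70% capture there, the range is 0 to 8 points. The direction depends only on capture being higher in the laser arms.

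This is a cheap improvement to safety data. It does not affect the primary endpoint or the sham-controlled comparison to Week 6.

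**What to change.** - Remove the restriction to ILM or SILM from the T2 enquiry.
- Put one identical scripted adverse-event question, with the same recall window, to all three arms at T1, T2, T3 and T4.
- State how monitoring between these assessments is done.
- Tabulate solicited and volunteered events separately by arm, so that extra session contact in the laser arms is visible.
- If the full protocol or Table 2 already does this, align Section 3.13 with it.

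The cost is one form item and a few minutes at each assessment, plus a few more background events on record. Section 3.7 lists the Week 3 assessment (T1), whereas Section 3.1 names only Baseline and Weeks 6, 12 and 18. The team should confirm that T1 is held in all arms, including waitlist, before relying on it. Treatment, endpoint and sample size are unchanged.

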### Criteria for discontinuation

3.14

Every effort will be made to retain patients in the trial and to minimize withdrawals. However, the trial will be discontinued on condition that any serious adverse events happen. Additionally, patients may request to be withdrawn from this study at any time without any reason.

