### Statistical analysis and sample size calculation

3.15

Standard descriptive statistics will be used to analyze baseline participant characteristics. We will produce summary statistics such as means, medians, standard deviations, and ranges for measured variables. We will tabulate frequencies for categorical and ordinal variables. We will use graphical methods extensively to examine distributions, identify potentially influential points, and guide data transformations if warranted. For continuous variables with markedly non-normal or skewed distributions, appropriate transformation may be required, such as natural logarithms, which we will apply as necessary and appropriate.^[43]^ In the sections below, we will assume, when discussing particular outcomes, that the appropriately transformed variables will be used. We will perform analysis according to the intention-to-treat (ITT) principle (i.e., subjects will be analyzed according to the treatment group to which they will be randomly allocated regardless of drop-out).

To determine the effects of ILM on fatigue, we will use mixed effects models.^[44]^ This statistical procedure takes into account within-subject correlations from repeated measurements in the same subjects and allows estimation of between-group difference without necessitating that the last observation is carried forward or exclusion of participants with missing data. Tests of ITT differences between intervention arms with respect to change in BFI-C will be based on time-intervention interactions in the mixed-effects models. Although randomization theoretically balances the potential confounders between treatment groups, occasional unequal distribution can be seen. Should this happen, the effect of confounding will be evaluated by including the potential confounders as co-variates in the models.^[43]^ For secondary outcomes, we will use similar analytical strategies for co-morbid symptoms. To evaluate the long-term durability of treatment effect, we will display long-term data descriptively. It is possible that the long-term outcome may display different patterns from short-term therapeutic effect. If this occurs, we may need to create piece-wise linear mixed-effects models to fit the data and test for statistical significance on outcome change among treatment groups.

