We have based our sample size calculation on our preliminary study. We plan to enroll and randomize 140 participants (2:2:1) to ILM, SILM, and WLC. Assuming a 20% attrition rate, we will have 45 participants in each of the ILM and SILM groups and 22 participants in the WLC group who will provide evaluable outcomes. In our previous study, we found that ILM produced a greater reduction in BFI-C intensity at the end of intervention (Week 4 from baseline) at a magnitude of 0.60 SD (Standard Deviation) as compared to SILM. Given an alpha of 5%, with 45 subjects in each of the ILM and SILM groups, we will be able to detect a between-group difference of reduction in BFI-C of 0.60 SD with 80% power. With 45 subjects each in the ILM and SILM groups and 22 participants in the WLC group, a power of 80% and two-sided alpha of 0.05, we will be able to detect an effect size of 0.71 SD (i.e., difference of reduction in BFI-C) between ILM and WLC or SILM and WLC groups. This is a conservative way to estimate sample size since the longitudinal analysis using all repeated measures with the mixed-effects model specified in the analysis plan will provide higher power than a *t* test.

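### Section 3.14 as written stops the whole trial at the first serious adverse event, whatever its cause or arm; a participant-level rule was probably meant and the sentence should be reworded

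*Protocol article*

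**What the plan says.** Section 3.14 (Criteria for discontinuation) has three sentences. The first concerns individual patients: "Every effort will be made to retain patients in the trial and to minimize withdrawals". The second, introduced as a contrast, says that "the trial will be discontinued on condition that any serious adverse events happen". The third returns to individuals: "Additionally, patients may request to be withdrawn from this study at any time without any reason".

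Section 3.13 (Assessment of adverse events) sets the scope of monitoring: "We will monitor patients for adverse events (AEs) during the study period and record any incidents in the case report forms". It adds a structured enquiry at T2 that asks patients "whether they have experienced or are experiencing AEs during the intervention (ILM or SILM) period", and it provides for causality: "The principal investigator or treating clinician will assign the attribution of the AEs".

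Section 3.15 commits to an intention-to-treat analysis in which "subjects will be analyzed according to the treatment group to which they will be randomly allocated regardless of drop-out", and gives the number exposed to the rule: "We plan to enroll and randomize 140 participants (2:2:1) to ILM, SILM, and WLC". Section 3.5.3 states that the waitlist arm receives neither real nor sham laser during the study.

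**The concern.** The operative sentence names the trial, uses a mandatory verb and is triggered by any serious adverse event. Attribution is assigned under section 3.13, but section 3.14 makes no use of it. Because section 3.13 monitors patients in general over the study period, an unrelated hospital admission in a waitlist participant would meet the trigger.

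Both possible readings cause trouble:

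- **Trial level.** A single event unconnected with the device ends the study. If it falls before the last Week 6 visit, the primary comparison may be left incomplete.
- **Participant level.** The text names the wrong object, so carrying on after a serious event would depart from the written protocol. The sentence also fails to separate stopping treatment from leaving the study. Participants who leave take with them later outcomes that the intention-to-treat analysis would want.

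**Working it through.** **Reading the text.** The sentence before it is about retaining patients and the sentence after it is about patients withdrawing on request. The contrast that opens the middle sentence and the link that opens the third both fit best if the middle one gives another reason for an individual to leave. Against that, the first sentence uses *the trial* in its ordinary sense, meaning the study in which patients are retained. Nothing elsewhere in the article narrows the rule by cause, arm, number of events or a review step. The participant-level reading is therefore likely, but it is an inference.

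**Size of the literal rule (illustration only).** The protocol states no serious adverse event rate and no stopping probability, so there is no figure to reproduce.

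Inputs from the protocol:

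- 140 randomized 2:2:1, so the waitlist arm has 140 × 1/5 = 28 (section 3.15)
- 20% attrition, leaving 0.8 × 140 = 112 (section 3.15)
- 6 weeks of treatment plus 12 weeks of follow-up, 18 weeks in all (section 3.1)
- recruitment from June 2018 to December 2019, taken as about 78 weeks (section 3.1)

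Assumptions: an 18-week risk p per participant of 0.1%, 0.5% or 1%; constant hazard; independent participants; even accrual.

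*Any event during follow-up.* P(at least one) = 1 − (1 − p)^n. The case n = 112 is a lower bound in which participants lost to attrition contribute nothing.

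| p | n = 140 | n = 112 |
|---|---|---|
| 0.1% | 0.131 | 0.106 |
| 0.5% | 0.504 | 0.430 |
| 1% | 0.755 | 0.676 |

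The risk at which the chance reaches 50% is 1 − 0.5^(1/n), which is 0.49% for 140 and 0.62% for 112.

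*Events before the last Week 6 visit.* With entry spread over 78 weeks, the last Week 6 visit falls at week 78 + 6 = 84. A participant entering in week e contributes min(18, 84 − e) weeks. Those entering in the first 66 weeks contribute all 18. Those entering in the last 12 weeks contribute between 18 and 6, on average 12. The mean is (66 × 18 + 12 × 12)/78 = 17.08 weeks, a fraction f = 17.08/18 = 0.949 of full follow-up. P = 1 − (1 − p)^(nf).

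| p | n = 140 | n = 112 |
|---|---|---|
| 0.1% | 0.124 | 0.101 |
| 0.5% | 0.486 | 0.413 |
| 1% | 0.737 | 0.656 |

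Taking accrual as 82 weeks changes these by at most 0.001.

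*Waitlist arm alone.* At p = 1%, 1 − 0.99^28 = 0.245: about a one-in-four chance that an event in a participant given no device treatment would trigger the rule. This assumes that events there are recorded as fully as elsewhere. The T2 enquiry covers only the real or sham treatment period, so ascertainment in this arm is thinner.

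**The case against.** The strongest reply is that context largely settles the meaning. A whole-trial stop would contrast with nothing in the sentence before it and would sit oddly with the one after it, so *the trial* is probably a loose way of saying participation in the trial. On that reading the severe consequence disappears, and section 3.15 already covers the analysis with intention to treat and a mixed model that does not exclude participants with missing data. The probabilities follow from assumed rates and so are not evidence of harm. Relatedness limits, review steps and stopping criteria often sit in a full protocol that is not shown.

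Much of this stands. The participant-level reading is the more likely one, and the figures show only how the literal rule behaves under stated assumptions. But the point is not that a stopping rule is missing. The article states one, without qualification, and a fuller document could only contradict it. A safety instruction should not need inference from its neighbours to be applied correctly. Nor does the mixed model dispose of the participant-level problem: it uses the data that exist, but it does not recover outcomes that were never collected because someone was taken out of the study.

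**Conclusion.** The concern holds. Section 3.14 states a mandatory rule on any serious adverse event, with no limit by relatedness or arm, and nothing else in the article qualifies it. Applied literally, it could close the trial on one unrelated event: about a 50% to 76% chance with 140 participants at an assumed 18-week risk of 0.5% to 1%, or 43% to 68% if only 112 contribute. Counting only events before the last Week 6 visit gives 49% to 74% and 41% to 66%. At an assumed 0.1%, all four figures are about 10% to 13%.

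These numbers rest on assumed rates, constant hazard, independence and, for the Week 6 figures, even accrual; the wording defect rests on none of them. It should be fixed. Confidence is medium because the intended meaning is inferred and investigators may not apply the sentence literally.

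**What to change.** Reword section 3.14 so that a serious adverse event leads to review and, where warranted, to discontinuation of that participant's study treatment. State that outcome follow-up continues after treatment stops, so that the participant's data remain available for the intention-to-treat analysis. Address closure of the whole trial separately, as something considered only after review of serious adverse events attributed to the intervention under section 3.13. The clinical criterion for that decision is for the sponsor and its safety oversight to set.

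The cost is a short protocol amendment confined to this one sentence. Sample size, endpoint and analysis do not change.
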